#### Criteria of comprehensive efficacy

(i)Criteria of cure: the evaluation of clinical symptoms reached the level of cure after seven days of treatment; the value of urine leukocytes returned to the normal value; the original infected bacteria was cleared after seven days of treatment. All three criteria must be met.(ii)Criteria of effective treatment: the clinical symptoms were alleviated but did not reach the level of cure after seven days of treatment; the value of urine leukocytes was reduced but not returned to normal after seven days of treatment. Either of these criteria must be met.(iii)Criteria of invalid treatment: the clinical symptoms were not alleviated after seven days of treatment; the value of urine leukocytes was still higher than normal after seven days of treatment; the original infected bacteria were still cultured from the original infection position after seven days of treatment. All three criteria must be met.

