## Method/design

### Objective and design

This is a randomized, double-blind, double-dummy, parallel control of positive drug, multicentre clinical study. The study will be conducted at: the XiYuan Hospital, China Academy of Chinese Medical Sciences; the Longhua Hospital Shanghai University of Traditional Chinese Medicine; the Guangdong Provincial Hospital of Traditional Chinese Medicine; the Hubei Hospital of Traditional Chinese Medicine; the Affiliated hospital of Chengdu University of Traditional Chinese Medicine; and the Yunnan Provincial Hospital of Traditional Chinese Medicine. Ethical clearance for the trial was obtained from ethics committee of the six hospitals. Patients with acute uncomplicated lower UTI will undergo a standardized baseline evaluation before treatment, comprising detailed history taking, physical examination, and laboratory testing. All included patients are randomly divided into three groups: experimental group; control group 1; and control group 2. The experimental group receives SJT plus levofloxacin tablets (LT) placebo; control group 1 receives LT plus SJT placebo; and control group 2 receives SJT plus LT on the first five days, SJT plus LT placebo on the last two days. After seven days of treatment, the efficacy and safety of three groups will be evaluated. The first aim is to determine whether SJT can reduce the use of antibiotics (control group 2 versus control group 1, non-inferiority test); the second aim is to determine whether SJT can substitute the use of antibiotics (experimental group versus control group 1, non-inferiority test). The recurrence rate will be assessed at the 28-day follow-up after being cured to determine whether SJT can reduce the recurrence rate. The trial is conducted in accordance with the World Medical Association Declaration of Helsinki and Good Clinical Practice of Pharmaceutical Products [17, 18]. After a full explanation by the clinicians, written informed consent will be obtained from the participants before intervention [19, 20]. Strict data management and quality control will be conducted in this trial [21, 22]. This trial was registered in the Clinical Trials USA registry (registration No. NCT03658291) on 4 September 2018 and will be carried out from January 2019 to December 2019. The study design is shown in Fig. 1. The protocol follows the recommendations of the SPIRIT initiative (see Additional file 1) [23] and the trial results will be reported according to the latest version of the CONSORT statement [24].

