#### Inclusion criteria

Inclusion criteria are as follows: (i) age > 18 and < 50 years; (ii) meet the western diagnostic criterion of acute uncomplicated lower UTI [26] that the disease duration does not exceed 72 h; (iii) bacterial culture result will be sensitive to levofloxacin (bacterial culture and clinical treatment will be conducted at the same time); (iv) the syndrome differentiation of TCM is syndrome of dampness-heat in the lower jiao; (v) did not receive antibiotic treatment within 48 h before being selected; (vi) not pregnant or lactating; and (vii) sign the written informed consent form for the clinical trial.

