## Outcome measures

### Effective rate

The effective rate will be evaluated from three dimensions: symptoms; urine leukocytes; and bacteriological examination.

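### The comprehensive class 'effective' carries no culture condition, so partial improvement with the original pathogen still growing at day 7 counts as effective treatment

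*Protocol article*

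**What the plan says.** The Effective rate section of the protocol article states: "The effective rate will be evaluated from three dimensions: symptoms; urine leukocytes; and bacteriological examination". The section Criteria of comprehensive efficacy then combines the three dimensions into three classes.

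- *Cure* requires symptom cure, normal leukocytes and clearance; its last condition reads "the original infected bacteria was cleared after seven days of treatment. All three criteria must be met".
- *Effective* begins "Criteria of effective treatment: the clinical symptoms were alleviated but did not reach the level of cure after seven days of treatment" and ends "the value of urine leukocytes was reduced but not returned to normal after seven days of treatment. Either of these criteria must be met". Culture does not appear.
- *Invalid* requires unrelieved symptoms, leukocytes above normal and persistence; its last condition reads "the original infected bacteria were still cultured from the original infection position after seven days of treatment. All three criteria must be met".

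According to the Inclusion criteria, the "bacterial culture result will be sensitive to levofloxacin". Objective and design says that "the second aim is to determine whether SJT can substitute the use of antibiotics", to be tested as non-inferiority of SJT alone to levofloxacin. Symptoms are the named primary measure of the effective rate (Abstract; Primary outcome measure). Clearance is assessed separately in all 252 participants (Secondary outcome measure, item ii).

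**The concern.** The comprehensive criteria are the only measure that brings all three dimensions together, so a reader will take a comprehensive effective rate to include bacteriology. In the middle class it does not. A patient with some relief and the original organism still in the urine receives the same grade as one with equal relief and a sterile culture.

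The ordering also goes wrong. With a persisting pathogen, a patient who is symptom-free with normal leukocytes has no class at all, while one who still has symptoms and raised leukocytes is 'effective'.

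The trial asks whether a herbal product can stand in for an antibiotic. If SJT clears the organism less often, a class that ignores culture shrinks the visible difference, and in a non-inferiority comparison a smaller difference favours the claim.

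**Working it through.** The point concerns a classification rule, so there is no planned figure to reproduce.

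**Step 1: apply the rules literally.** Symptoms and leukocytes have three levels each and culture has two, which gives 18 patterns.

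| Symptoms | Leukocytes | Pathogen cleared | Pathogen persists |
|---|---|---|---|
| cured | normal | cure | no class |
| cured | reduced, not normal | effective | effective |
| cured | not reduced | no class | no class |
| alleviated | normal | effective | effective |
| alleviated | reduced, not normal | effective | effective |
| alleviated | not reduced | effective | effective |
| not alleviated | normal | no class | no class |
| not alleviated | reduced, not normal | effective | effective and invalid |
| not alleviated | not reduced | no class | invalid |

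With a persisting pathogen: 5 of 9 meet 'effective' (4 cleanly, 1 also 'invalid'), 1 is only 'invalid' and 3 have no class. The same five rows are 'effective' whatever the culture shows. Culture changes cure-or-effective status in one row only, the first.

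**Step 2: what the rule adds to a rate.** Suppose cure and effective are pooled; the article does not say so. Against a rule that also demands clearance, the pooled rate in an arm is higher by exactly the share of that arm's patients who are 'effective' with a persisting pathogen. The dilution of the arm difference is the difference between arms in that share. This identity needs no distributional assumption. Its size does.

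**Step 3: illustration A.** All inputs are assumptions: symptoms cured/alleviated/not alleviated 50/35/15%; leukocytes normal/reduced/not reduced 55/30/15%; domains independent and equal in both arms; clearance p = 0.90 versus 0.50; the overlapping pattern counted as effective.

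- Cure = 0.50 × 0.55 × p = 0.275p.
- Effective = 1 − (1 − 0.35)(1 − 0.30) = 0.545, whatever p is.
- As written: 0.2475 + 0.545 = 0.7925 versus 0.1375 + 0.545 = 0.6825, a gap of 11.0 points.
- Clearance required: (0.275 + 0.545)p = 0.82p, so 0.738 versus 0.410, a gap of 32.8 points.
- If the overlapping pattern (0.15 × 0.30 = 0.045) goes to 'invalid' when the pathogen persists: 0.7925 − 0.045 × 0.10 = 0.788 versus 0.6825 − 0.045 × 0.50 = 0.660, a gap of 12.8 points.

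**Step 4: illustration B.** Assumed: 15% clinical non-responders, the same clearance rates independent of clinical response, and a share q of patients symptom-free with normal leukocytes. Patients without a class count as non-responders. The rate as written is qp + (1 − q − 0.15); with clearance required it is 0.85p.

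| q | As written | Gap (points) | Clearance required | Gap (points) |
|---|---|---|---|---|
| 0.10 | 84% vs 80% | 4 | 76.5% vs 42.5% | 34 |
| 0.30 | 82% vs 70% | 12 | 76.5% vs 42.5% | 34 |
| 0.50 | 80% vs 60% | 20 | 76.5% vs 42.5% | 34 |
| 0.70 | 78% vs 50% | 28 | 76.5% vs 42.5% | 34 |

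If symptom-free patients with normal leukocytes and a persisting pathogen are instead counted as effective, the rule gives 85% versus 85%, a gap of 0.

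**Step 5: what the illustrations leave out.** Both hold symptoms and leukocytes equal across arms and independent of culture. If persisting infection shows itself as persisting symptoms or raised leukocytes, part of the difference returns through those two dimensions. At the extreme, where every patient with a persisting pathogen is unrelieved with unreduced leukocytes, none is 'effective' and nothing is diluted.

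**The case against.** The strongest reply is that the comprehensive criteria are not shown to carry the trial's conclusion. The primary measure is symptoms. The section defining the comprehensive classes calls them neither primary nor secondary, and no passage ties them to the non-inferiority test or pools cure with effective. The Sample size section calls the effective rate the main outcome without saying which version. Failure to clear would still appear in the separate secondary outcome. A middle grade for clinical improvement without clearance can also be a deliberate choice, and the three dimensions announced under Effective rate are each assessed somewhere, so this is not a strict contradiction.

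Most of that stands, and it limits the consequence. A reader might infer that the comprehensive rate is nearly blind to failure to clear, or that it hides two thirds of a difference (illustration A: 11.0 of 32.8 points remain). The documents support neither as a quantity. They give no clearance rates and no joint distribution, and the residual gap moves from 0 to 28 points with the assumptions. That clearance is where the arms will differ most is likewise an inference.

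The reply does not explain the ordering. A deliberate middle grade would not leave the symptom-free patient with normal leukocytes and a positive culture without a class while grading a symptomatic one as effective.

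**Conclusion.** The point holds as a defect of the rule. 'Effective' ignores culture, and five of nine persisting-pathogen patterns qualify, four of them unambiguously. If cure plus effective is used to support substitution and SJT clears less often, a difference in clearance is diluted and the comparison leans towards non-inferiority wherever improved patients with a persisting pathogen are commoner on SJT. The size cannot be derived from the protocol.

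A reader might go further and conclude that the trial's non-inferiority result is biased. The text does not support that, because the named primary outcome is symptoms and clearance is reported in its own right. This is a cheap improvement, between worth considering and advisable, and not a condition for the trial to be interpretable.

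**What to change.** In Criteria of comprehensive efficacy, split 'effective' by day-7 culture into *improved, pathogen cleared* and *improved, pathogen persisting*, and report both in every arm. Count only the cleared part, with cure, in any comprehensive effective rate used to support substitution.

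Assign every remaining persisting-pathogen pattern to a stated non-effective class, including symptoms cured with normal leukocytes. State one class for the pattern that now meets both 'effective' and 'invalid'. The three unclassified rows with the pathogen cleared also need a place if the classes are to be exhaustive. Simply adding clearance to the 'effective' rule is not enough: it would leave seven of the nine persisting-pathogen patterns without a class, against three now.

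The cost is wording and one derived variable, since the culture is already planned for all 252 participants. The comprehensive rate will fall, possibly a good deal where clearance is low: in illustration A at 50% clearance, 0.6825 − 0.410 = 0.2725, about 27 points, against 0.7925 − 0.738 = 0.0545, about 5 points, at 90%. It should therefore not be compared directly with the 77.14% planning figure in the Sample size section.

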**Methods/design:**

In this study, a randomized, double-blind, double-dummy, parallel control of positive drug, multicenter clinical study will be established. A total of 252 patients with acute uncomplicated lower UTI (syndrome of dampness-heat in the lower jiao) will be randomly allocated in the ratio of 1:1:1 to three groups: experimental group; control group 1; and control group 2. The experimental group receives Sanjin tablets plus levofloxacin tablets (LT) placebo; the control group 1 receives LT plus SJT placebo; and the control group 2 receives SJT plus LT on the first five days, SJT plus LT placebo on the last two days. Each group will be treated for seven days and followed-up 1–2 times. The primary outcome measures of effective rate and recurrence rate are symptoms. Secondary outcome measures of effective rate and recurrence rate are the urine leukocytes, bacteriology examination, and safety assessment. Outcomes will be assessed at baseline and after treatment.

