### Sample size

The effective rate will be taken as the main outcome measure of the clinical trial. According to a previous study, it showed that the effective rate of SJT was 77.14% in the treatment of simple bacterial lower urinary tract infection [25]. On the basis of a 0.9 power to detect a significant difference (α = 0.01, two-sided), 76 participants will be required for each group. 228 participants will be required for the three groups in a 1:1:1 ratio. Considering a 20% drop-out rate, we plan to include 252 patients in the whole trial.

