#### Secondary outcome measure

(i)The urine leukocytes of 252 participants will be assessed. If the value of urine leukocytes is returned to normal after seven days of treatment, it indicates the patient is cured. If the value of urine leukocytes is reduced but not returned to normal after seven days of treatment, it indicates that the treatment is effective. If the value of urine leukocytes is still higher than the normal value after seven days, it indicates the treatment is invalid.(ii)The bacteriological examination of 252 participants will be assessed. If the original infected part of the specimen did not regenerate the original infected pathogen after seven days of treatment, it indicates the original bacteria is cleared. If the original pathogen was still cultured in the culture of the specimen from the original infection position, it indicates the original bacteria is not cleared.

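### Any fall in urine leukocytes short of normal, however small, counts as effective and is enough alone in the comprehensive rule; the same patient can also be classed invalid

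*Protocol article*

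**What the plan says.** All places are in the protocol article.

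- **Secondary outcome measure (effective rate), item (i).** A partial fall is a success: "If the value of urine leukocytes is reduced but not returned to normal after seven days of treatment, it indicates that the treatment is effective". The next sentence of the same item reads: "If the value of urine leukocytes is still higher than the normal value after seven days, it indicates the treatment is invalid".
- **Criteria of comprehensive efficacy, item (ii).** There are two limbs. The symptom limb is "the clinical symptoms were alleviated but did not reach the level of cure after seven days of treatment". The leukocyte limb and the rule joining the two are "the value of urine leukocytes was reduced but not returned to normal after seven days of treatment. Either of these criteria must be met". Bacteriology plays no part in (ii).
- **Criteria of comprehensive efficacy, items (i) and (iii).** Cure needs all three dimensions to succeed. Invalid needs all three to fail, and its leukocyte element is a value still above normal.
- **Role of each outcome.** The abstract says "The primary outcome measures of effective rate and recurrence rate are symptoms" and "Secondary outcome measures of effective rate and recurrence rate are the urine leukocytes, bacteriology examination, and safety assessment". The Sample size section says "The effective rate will be taken as the main outcome measure of the clinical trial" without naming a dimension, and the Effective rate section says that rate has three dimensions. The comprehensive rule is not labelled primary or secondary.
- **Type of comparison.** Both antibiotic aims are non-inferiority comparisons with control group 1; the second is "experimental group versus control group 1, non-inferiority test". The article gives no margin.

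**The concern.** The leukocyte limb amounts to this: normal limit < day-7 value < baseline value. It contains no minimum change, so measurement variation alone can satisfy it. The symptom criteria are stricter by comparison: under Primary outcome measure, improvement on the urinary infection severity sheet needs a move of a whole severity band.

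In a superiority trial a lenient responder rule mostly costs power. In a non-inferiority trial it works in favour of the conclusion. If the same share of failures is relabelled as effective in every arm, the arms look more alike and a real deficit of Sanjin tablets against levofloxacin is easier to miss.

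The rule also fails to give each patient one class. Where two classes apply, or none, the effective rate depends on a choice that the article does not make and that could be made after the data are seen.

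**Working it through.** **Step 1. Apply the comprehensive rule to concrete patients.**

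| Symptoms | Leukocytes at day 7 | Original pathogen | Effective (ii)? | Invalid (iii)? | Class |
|---|---|---|---|---|---|
| not alleviated | slightly lower, still abnormal | cleared | yes | no | effective |
| not alleviated | slightly lower, still abnormal | persists | yes | yes | both |
| not alleviated | normal | persists | no | no | none |

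The first row shows the threshold problem without any overlap: only (ii) applies. In the leukocyte outcome, every count that is lower but still abnormal is both effective and invalid.

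**Step 2. How often could noise satisfy the leukocyte limb?** The article gives no figure to reproduce and no leukocyte distribution, so this is an assumed range. Model: baseline b and day-7 value d on the log scale, standard normal, no true change, repeat correlation ρ from 0.3 to 0.9.

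If patients enter whenever b exceeds the normal limit L, the two readings are exchangeable and

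P(L < d < b | b > L) = ½ · P(d > L | b > L).

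Half is then the ceiling.

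- *L at the population mean.* P(d > 0 | b > 0) = ½ + arcsin(ρ)/π. At ρ = 0.3 this is 0.597, so the limb is met in 0.30. At ρ = 0.9 it is 0.856, so 0.43.
- *L at 1 SD above the mean.* By numerical integration, 0.14 at ρ = 0.3 and 0.36 at ρ = 0.9.
- *Entry at 1 SD above the mean, L at the mean (entry values well above normal).* 0.54, 0.61, 0.65 and 0.63 at ρ = 0.3, 0.5, 0.7 and 0.9.

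The scenarios span about 14–65%. They are illustrations, not bounds: the result depends on how far entry values lie above normal.

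**Step 3. Effect on a comparison.** If a fraction f of true failures is credited as effective in each arm, the observed rate is p + (1−p)f and the observed difference is (1−f) times the true one.

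Assumed inputs: true rates 90% v 70%, a 15-point margin and a two-sided 95% Wald interval. From the document: 252/3 = 84 per arm. Exact binomial enumeration gives:

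| f | Observed rates | Observed deficit | P(non-inferiority declared) |
|---|---|---|---|
| 0 | 90% v 70% | 20 points | 0.3% |
| 0.3 | 93% v 79% | 14 points | 5% |
| 0.4 | 94% v 82% | 12 points | 10% |
| 0.5 | 95% v 85% | 10 points | 22% |

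For example, at f = 0.4: 0.70 + 0.30 × 0.4 = 0.82, 0.90 + 0.10 × 0.4 = 0.94, and the difference is 0.12 = 0.6 × 0.20.

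A second set of assumptions points the same way. With 76 per arm, a 20-point margin, one-sided 0.025 and true rates of 77.1% v 57.1%, the normal approximation gives 2.5% at f = 0, 14% at f = 0.3, 24% at f = 0.4 and 39% at f = 0.5.

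**The case against.** Four points can be made for the plan.

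1. *The main conclusion may be untouched.* Symptoms are the named primary outcome and leukocytes are secondary, and no section assigns the non-inferiority tests to the comprehensive rate. This stands. A reader might infer that the primary non-inferiority claim is compromised, but the documents support that only if the effective rate in the Sample size section is the comprehensive one. The wording leaves this open.

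2. *Noise need not be large.* A reader might infer that an ineffective treatment would be scored effective at least half the time. The documents do not support this. It treats the limb as any fall, which under Step 2's model with entry at the mean or 1 SD above it occurs in 57–86%. The limb as written excludes counts that reach normal. It passes half only when entry values lie well above normal, or when chance symptom relief is added, and the article quantifies neither. Reclassifying 75% of failures, which would give 81% false non-inferiority in Step 3's model, needs symptom relief to arise by chance in half of patients. Nothing in the article supports that.

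3. *A patient with unchanged symptoms and a persisting pathogen is not simply effective.* Correct: with an abnormal count, that patient also meets invalid. If invalid took precedence, the leukocyte outcome would have no partial success at all. But the patient whose pathogen is cleared meets only the effective class of the comprehensive rule, so the missing threshold is not just a by-product of the overlap.

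4. *Strict definitions already exist.* Leukocyte cure and comprehensive cure are both demanding. That is so, but the plan reports an effective rate and nothing confines the comparisons to cure.

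**Conclusion.** The point holds as a defect in two stated definitions, and its effect on the trial's conclusion is conditional. What follows from the text alone: there is no minimum fall, one limb suffices, and the effective and invalid classes overlap in both the leukocyte outcome and the comprehensive rule, with some patients left unclassified.

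The size rests on assumptions. These are the leukocyte model behind the 14–65% range, equal crediting of failures in all arms, and the illustrative rates and margin behind the rise from 0.3% to 5–22%. The direction, towards non-inferiority on the leukocyte and comprehensive rates, needs only that failures be credited in similar proportion across arms. The definitions should be corrected before unblinding. The documents do not show that the symptom-based primary analysis is biased.

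**What to change.** - Take the plan's existing criterion, return to normal, as the yes/no leukocyte response. Report the size of the fall as a continuous, baseline-adjusted measure.
- In the comprehensive rule, remove the provision that a leukocyte fall alone qualifies as effective.
- Reword effective and invalid together, in both the leukocyte outcome and the comprehensive rule, so that every patient falls into exactly one class. Changing effective alone would leave more patients unclassified.
- State whether the effective rate in the non-inferiority tests is the symptom rate or the comprehensive rate.

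The cost is a change of wording before unblinding, with no new measurements. The downside is a lower headline effective rate in every arm.

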#### Primary outcome measure

The symptoms of acute uncomplicated lower UTI will be assessed. The assessment tools for symptoms of acute uncomplicated lower UTI are three participant self-rating scales (see Additional file 2): criteria sheet for evaluating the severity of urinary system infection (CSESUSI; mild: total score ≤ 8, moderate: total score 9–15, severe: total score ≥ 16), if the severity of the disease decreases from severe to moderate, or from moderate to mild, the symptoms are improved; symptoms score sheet of TCM (SSST; cure: total score = 0, effective: total score 0–6, invalid: total score ≥ 6); overactive bladder symptom score (OABSS; if the urgent urination score > 2 and total score > 3, OAB will be diagnosed; mild: total score ≤ 5, moderate: total score 6–11, severe: total score ≥ 12). The CSESUSI will use a scoring method to record the changes of symptoms and signs before and after treatment, such as shivering, fever, dysuria, urinal pain, urinary urgency, urinary frequency, lower abdomen distending pain, lumbago, and percussion tenderness over kidney region. The SSST uses a scoring method to record the changes of symptoms, tongue, and pulse in TCM before and after treatment. The OABSS has been found to be reliable and valid and highly responsive to treatment-related fluctuations in overactive bladder symptoms. Repeating the test after an acceptable treatment interval is an effective way to assess the efficacy of a particular drug regimen on OAB symptoms [33, 34]. If the symptoms disappeared after seven days of treatment, it indicates that the patient is cured. If these symptoms partially disappeared after seven days of treatment, it indicates that the treatment is effective but not cured. If there was no obvious remission and the symptoms of infection persisted after seven days of treatment, it indicates that the treatment is invalid.

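### The comprehensive efficacy classes leave 6 of 18 possible day-7 patterns without a class and put one pattern in two classes

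*Protocol article*

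**What the plan says.** The section Criteria of comprehensive efficacy gives three rules.

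- **Cure** joins three conditions, ending with "the original infected bacteria was cleared after seven days of treatment. All three criteria must be met".
- **Effective** lists two partial results: symptoms better but not gone, and leukocytes lower but still abnormal. It closes with "Either of these criteria must be met". Culture plays no part.
- **Invalid** joins three failures, ending with "the original infected bacteria were still cultured from the original infection position after seven days of treatment. All three criteria must be met".

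The section gives no order of precedence and no class for other patients.

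The levels come from the two preceding sections under Effective rate. Primary outcome measure has three symptom levels. The best level is defined by "If the symptoms disappeared after seven days of treatment, it indicates that the patient is cured". For the middle level, the wording is "If these symptoms partially disappeared after seven days of treatment, it indicates that the treatment is effective but not cured". The worst level, called invalid, starts "If there was no obvious remission and the symptoms of infection persisted after seven days of treatment". Secondary outcome measure has three leukocyte levels. The normal level is defined by "If the value of urine leukocytes is returned to normal after seven days of treatment, it indicates the patient is cured". For the intermediate level, the condition is "If the value of urine leukocytes is reduced but not returned to normal after seven days of treatment". The third level is a value still above normal. Culture has two results, cleared or not cleared.

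**The concern.** Cure and invalid each require agreement across all three domains, and both effective limbs exclude full resolution. A patient who does well in one domain and badly in another can therefore fall between the rules. One example is a patient with no symptoms and normal leukocytes whose original pathogen still grows. The culture rules out cure, full resolution rules out both effective limbs, and symptom relief rules out invalid.

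The comprehensive effective rate cannot be computed for such patients without a further rule. If that rule is chosen after the data are seen, the choice can shift the result. The trial's two comparisons with control group 1 are non-inferiority comparisons, where lenient handling of doubtful outcomes needs care.

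**Working it through.** The document gives no count for this classification, so there is no stated figure to reproduce. The check is a full enumeration.

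**Inputs.** Symptoms: gone, partly relieved, not relieved (Primary outcome measure). Leukocytes: normal, reduced but abnormal, not reduced (Secondary outcome measure). Culture: cleared, not cleared (same section). Patterns: 3 × 3 × 2 = 18.

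**Rules, read literally.** Cure = gone AND normal AND cleared. Effective = partly relieved OR reduced but abnormal. Invalid = not relieved AND above normal AND not cleared. A reduced but abnormal value is still above normal.

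| Symptoms | Leukocytes | Cleared | Not cleared |
|---|---|---|---|
| Gone | Normal | Cure | **none** |
| Gone | Reduced, abnormal | Effective | Effective |
| Gone | Not reduced | **none** | **none** |
| Partly relieved | Normal | Effective | Effective |
| Partly relieved | Reduced, abnormal | Effective | Effective |
| Partly relieved | Not reduced | Effective | Effective |
| Not relieved | Normal | **none** | **none** |
| Not relieved | Reduced, abnormal | Effective | **Effective and invalid** |
| Not relieved | Not reduced | **none** | Invalid |

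**Count.** 1 cure + 9 effective only + 1 invalid only + 1 in two classes + 6 in none = 18.

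**Other readings.** If above normal is taken to exclude values that have fallen, the overlap disappears (10 effective, 1 invalid) but 6 patterns still have no class. If the effective limbs are read as exclusive alternatives, the number without a class rises to 8. No reading tried closes the gap. The leukocyte rule in Secondary outcome measure has the same overlap, because a lower but abnormal value meets both its effective and its invalid wording.

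**Ordering.** Partly relieved, not reduced, not cleared is effective. Gone, normal, not cleared is no worse in any domain and better in two, yet has no class.

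**Size.** Let an arm have n patients, s clear successes and k in the patterns without a single class, with u = k/n. Counting the k as failures gives s/n, and counting them as successes gives (s + k)/n. The difference is k/n = u. Dropping them gives s/(n − k), which lies between the two. With n = 252/3 = 84 and u assumed:

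- u = 2%: 0.02 × 84 = 1.7 patients, up to 2 points
- u = 5%: 0.05 × 84 = 4.2 patients, up to 5 points
- u = 10%: 0.10 × 84 = 8.4 patients, up to 10 points

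The document gives no basis for choosing u in any arm.

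**The case against.** The strongest reply is that the primary endpoint does not use these classes. The Abstract names symptoms as the primary measure, and Primary outcome measure has its own symptom-only rule with no reference to the comprehensive criteria. This stands, and it limits the point to the comprehensive rate. It is not a full answer, because Sample size calls the effective rate the main outcome without saying which one, and the opening of Effective rate says it is judged on all three dimensions.

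A second reply is that a condensed article may leave a remainder rule to the full protocol or analysis plan. Such a rule may exist. But the article does not merely omit detail: it prints complete rules, and an analysis that followed them would inherit the gap.

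A reader might go further in three ways that the document does not support.

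- *That every symptom-free patient with a persisting pathogen is unclassified.* Only two of the three such patterns are. The third, with leukocytes reduced but abnormal, is effective. Of the other four patterns without a class, three have unrelieved symptoms and one has symptoms gone and the pathogen cleared.
- *That the gap falls mainly on the experimental group because it receives no active levofloxacin.* This is plausible, but it is an inference. No passage gives expected culture results by arm, and Background reports antibacterial activity of Sanjin tablets in mice.
- *That the arm difference shifts by a definite amount.* Assuming 8 and 2 unclassified patients among 84 per arm gives a shift of (8 − 2)/84 = 7.1 points between counting them as failures and as successes. That only restates the assumption; equal numbers would give no shift. Dropping the patients would also conflict with the intention-to-treat set in Data analysis, which is all randomized patients.

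**Conclusion.** The point holds for the comprehensive classification. Under the literal rules 6 of 18 patterns have no class, one has two, and the ordering is inconsistent. The count of 6 does not depend on how above normal is read, and it rests only on the levels that the document defines. It counts patterns, not patients. The effect on an arm's comprehensive effective rate is at most the share of that arm in these patterns: 2 to 10 points if that share is 2% to 10%, which is assumed.

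The symptom-only primary classification is not affected, and no bias between arms can be quantified. This is a defect in a supporting composite that should be corrected before unblinding. It would matter more if the effective rate in Sample size were meant to be the comprehensive one.

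**What to change.** Before unblinding, reword Criteria of comprehensive efficacy as ordered classes that place each patient once and keep both limbs:

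- **Cure:** all three domains resolved.
- **Effective:** not cure, and symptoms at least partly relieved (including gone) or leukocytes at least reduced (including normal).
- **Invalid:** every other patient.

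Invalid then holds only patients with unrelieved symptoms and unreduced leukocytes: 1 × 1 × 2 = 2 patterns. The split is 1 cure, 15 effective (18 − 1 − 2) and 2 invalid, and no better result gets a worse class. A rule based on symptoms alone would also be exhaustive, but it would remove the leukocyte limb and merely repeat the primary outcome.

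This rule is lenient towards patients whose pathogen persists, which matters in a non-inferiority comparison. So report pathogen persistence within each class by arm, and add a sensitivity analysis that counts patients with a persisting pathogen as failures. In Secondary outcome measure, remove the overlap between the effective and invalid leukocyte levels. In Sample size, state that the main effective rate is the symptom-based one in Primary outcome measure.

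The cost is rewording and a little more analysis, with no new data. The comprehensive effective rate may move in either direction, depending on how the unclassified patients would otherwise have been handled.
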